## Abstract

Antidepressants are standardly used to treat moderate to severe symptoms of depression and/or anxiety in youth but may also be associated with rare but serious psychiatric adverse events such as irritability, agitation, aggression, or suicidal ideation. Adverse events are especially common in youth with a family history of bipolar disorder (BD) who are at heightened risk for dysfunction in neurobiological systems that regulate emotion and arousal. To further understand this phenomenon, this study will examine (a) baseline risk factors associated with dysfunctional arousal in a sample of youth at high-risk for BD treated with or without an antidepressant, (b) whether antidepressant-related changes in arousal are mediated by changes in prefrontal-limbic circuitry, and (c) whether pharmacogenetic factors influence antidepressant-related changes in arousal. High-risk youth (aged 12–17 years with moderate to severe depressive and/or anxiety symptoms and at least one first-degree relative with bipolar I disorder) will be randomized to receive psychotherapy plus escitalopram or psychotherapy plus placebo. Neuroimaging and behavioral measures of arousal will be collected prior to randomization and at 4 weeks. Samples for pharmacogenetic analysis (serum escitalopram concentration, *CYP2C19* metabolizer phenotype, and *HTR2A* and *SLC6A4* genotypes) will be collected at 8 weeks. Youth will be followed for up to 16 weeks to assess change in arousal measures.

## 1. Introduction

### 1.1. Risk Factors and Putative Mechanisms Underlying Emotional and Physiological Arousal during Antidepressant Treatment

Antidepressants are among the most common medications prescribed to youth in the United States (U.S.) and are used to treat many psychiatric disorders including depression and anxiety disorders [1]. The combined prevalence of depressive and anxiety disorders in U.S. adolescents is approximately 17% [2]. Multiple studies suggest that these medications reduce symptoms [3,4], improve functioning [5], and are generally well tolerated. However, several studies suggest that some youth may experience antidepressant-related psychiatric adverse events [6] such as aggression, psychosis, agitation, suicidal ideation, hypomania, or mania—all behaviors that may be associated with increased emotional arousal [7]. These adverse events are more frequent and potentially more severe in children compared to adults [8,9,10]. We might avoid some of these rare but serious adverse events by identifying youth who are at a greater risk of developing them.

Of particular interest to our study, youth with a family history of BD (i.e., “high-risk” youth) may be predisposed to developing antidepressant-related adverse events. This increased risk may relate to several factors, including increased vulnerability to developing dysfunctional emotional arousal, independent of antidepressant exposure. Indeed, a family history of BD is among the strongest risk factors for developing mood and anxiety disorders in youth [11]. Twin and family studies have provided compelling evidence that having a parent with BD [12,13] is associated with increases in risk for the offspring’s development of disorders of emotional arousal compared with the general population. Moreover, when these offspring develop dysfunctional emotional arousal, their risk of developing BD increases even further [14]. We now also know that multiple genes may moderate the association between having a parent with BD and an offspring’s development of BD [15], and that even healthy youth who have a parent with BD have distinct prefrontal, striatal, and limbic function and connectivity at rest [16], and during emotional [17] and reward processing [18] compared with healthy offspring of depressed and healthy parents. Taken together, these data suggest that neurogenetic vulnerabilities for developing BD precede symptom onset and may progress to manic symptom emergence and the onset of BD.

Antidepressants are commonly used to treat mood and anxiety symptoms [19], which in youth at risk for developing BD may represent prodromal manifestations of BD [8,20]. Therefore, it is difficult to disentangle whether the natural progression of prodromal manifestations and/or antidepressant-related dysfunction leads to the initial onset of manic or hypomanic symptoms. Moreover, whether antidepressants are safe and effective for youth with a family history of BD who present with depressive and anxiety disorders (but with no hypomania or mania symptoms), remains an ongoing clinical dilemma. Further complicating this problem are inconclusive results from intervention studies. Specifically, a few open-label studies in high-risk youth have examined the efficacy of pharmacologic agents including aripiprazole [21], lithium [22], divalproex [23], and quetiapine [24] for a variety of complex mood symptoms, but to date there are no large randomized controlled trials of antidepressants in youth with a family history of BD. Thus, understanding the risk factors for antidepressant-induced adverse events could guide clinicians to either avoid antidepressants or use different monitoring procedures in high-risk youth.

Studies reporting antidepressant-induced adverse events across multiple units of analysis have mechanistically implicated the Arousal construct of the Research Domain Criteria (RDoC) Arousal and Regulatory Systems. RDoC is a research framework for investigating psychiatric disorders that integrates many levels of information (e.g., genomics, neural circuits, behavioral ratings) to explore basic dimensions of functioning that span normal and abnormal human behavior. Arousal facilitates one’s interaction with the environment in a context-specific manner, can be modulated by the physical characteristics and motivational significance of stimuli, and can be regulated by homeostatic drives [25]. In humans and other animals, antidepressants may produce sustained changes in (1) behavioral [6,26] and psychophysiological indexes of arousal including increased emotional, sensory, and motor reactivity [27,28], (2) heart and respiratory rate [29], and (3) structure and function of regions involved in prefrontal-limbic circuits implicated in the generation [30] and regulation of emotional arousal [31]. Indeed, these changes have been observed in individuals with a genetic propensity for rare but serious adverse events from antidepressant exposure (e.g., mania, suicidality) [20]. They also span a range of psychiatric disorders [32], and this cascade of hyperarousal is especially pronounced in youth with a family history of BD [33,34].

With these consideration in mind, our double-blind placebo-controlled study will examine whether specific biomarkers predict the risk of antidepressant-induced hyperarousal and characterize the mechanisms underlying hyperarousal. Several mechanistic hypotheses may explain why some youths are more likely to develop adverse events while others benefit from antidepressants. First, antidepressants may be working to potentiate rather than attenuate a limbic system that may already be primed for reactivity in youth prone to adverse events [35]. Second, youth prone to arousal events may have modified gene expression of monoamine transporters that make it challenging for antidepressants to reach their typical neural targets [36]. Third, in contrast to the expected antidepressant-related decreases in limbic activity, adverse event-related limbic hyperactivity may occur with high antidepressant doses and acute dose escalations [37]. Finally, there are sensitive periods in development (e.g., puberty) when youth may be more vulnerable to antidepressant-related adverse events because of pruning of neural networks [38]. Through a combination of clinical trial design, functional neuroimaging, and pharmacogenetic analysis, we hope to generate data to better inform our understanding of each of these explanations.

### 1.2. Dynamic Functional Networks Subserving Hyperarousal

Neural systems involved in sensory (e.g., amygdala) and emotion regulatory function (e.g., ventral lateral prefrontal cortex, VLPFC) are implicated in emotional arousal. Neural models of adults [39,40] and children [41,42] with symptoms of disrupted emotional arousal across multiple psychiatric syndromes posit broader aberrant interactions between regulatory structures and sensory structures that support the generation and regulation of emotional arousal [43]. These studies suggest that aberrant emotional arousal is associated with dysfunction in a prefrontal-limbic circuit through impaired top-down prefrontal regulation of bottom-up limbic hyperactivity [44,45]. In adults and youth, antidepressants appear to exert their therapeutic effects, in part, by normalizing this aberrant functional activation [46,47,48]. Over time, antidepressants may initially increase [49] and then decrease amygdala activity while increasing prefrontal inhibition of the amygdala. In contrast, one study identified a significant difference in mean activation in the right amygdala among youth with a familial risk for bipolar disorder treated with antidepressants, at-risk youth without antidepressant use, and healthy controls. Specifically, youth at risk for bipolar disorder who were treated with antidepressants and experienced an antidepressant-related adverse reaction had the lowest amygdala activation at baseline [50]. These findings suggest that in youth at risk for bipolar disorder, baseline dysregulation of amygdala activity may be exacerbated by antidepressants and inadequately moderated by prefrontal regulation of amygdala activity, leading to adverse behavioral reactions such as aggression, impulsivity, and irritability [50]. Though replicable findings describe consistent patterns of neural activity and modulation, antidepressants may exert dynamic effects on the brain which require repeated assessment over time.

Other studies have documented antidepressant-related aberrant physiological responses [29,51] and cardiorespiratory decoupling [52] that may be associated with dysfunctional arousal, independent of dosage or symptom severity [53]. Importantly, these patterns of neurobiological dysfunction can persist into adulthood, conferring lifelong vulnerabilities for the development of various psychopathologies [54,55]. Thus, individuals with specific neurobiological characteristics [56] may be at relatively higher risk for antidepressant-related hyperarousal. To date, however, research has been limited to examining risk factors retrospectively, using small samples [57,58], and assessing unitary measures and categorical outcomes. The large, double-blind, placebo-controlled study described herein is designed to address these limitations by using an RDoC organizational framework. 

### 1.3. Escitalopram Pharmacogenetics in High-Risk Youth

Our study will use escitalopram, a selective serotonin reuptake inhibitor (SSRI), which is commonly used to treat depressive and anxiety disorders in children and adolescents [59]. Escitalopram is safe and effective for treating pediatric major depressive and generalized anxiety disorders [60], and is approved by the US Food and Drug Administration (USFDA) for the treatment of major depressive disorder in youth ages 12 and older. Additionally, escitalopram is well-tolerated and cost-effective [61,62]. Given the previously noted risks of developing any psychopathology [54] and/or experiencing a hyperarousal event in response to SSRIs [8,20] among youth at risk for BD, pharmacogenomic assays may provide targeted information about risks for adverse events in these youth (including hyperarousal) during treatment with escitalopram [63]. Modern genetic testing allows for quick genotyping for dozens of genetic polymorphisms which are identified as potential genes of interest in predicting treatment outcomes and rates of adverse events during treatment with escitalopram.

In this study, we will obtain a genetic sample from all high-risk youth to identify pharmacokinetic and pharmacodynamic risk alleles. Pharmacokinetic genes of interest include enzymes involved in the metabolism of escitalopram, including members of the cytochrome P450 (CYP) family, such as *CYP2C19*, *CYP2D6*, and *CYP1A2* [33,63,64]. CYP2C19 plays a significant role in the metabolism of escitalopram, and multiple single nucleotide polymorphisms (SNPs) in *CYP2C19* are linked to differences in the rate of escitalopram metabolism [65,66]. Multiple studies suggest that escitalopram dosing regimens should be modified based on *CYP2C19* alleles to achieve comparable therapeutic serum concentrations of escitalopram, as some genotypes confer a greater risk of therapeutic failure or adverse events [64,65,66,67]. Notably, individuals with BD, as compared to those with MDD, have poorer metabolism via CYP2C19, which may predispose them toward antidepressant-induced hyperarousal [68] (see Figure 1). Among adolescents with anxiety disorders treated with escitalopram who experienced hyperarousal, a greater maximum concentration (C_max_) and area under the curve (AUC) of blood serum concentrations of escitalopram was observed compared with adolescents who did not experience hyperarousal symptoms [64].

Other cytochrome P450 genes may also be involved in the metabolism of escitalopram, and some models suggest that pharmacogenomic assays which can integrate the influence of multiple CYP genes may have greater therapeutic utility than a focus on any one CYP gene involved in escitalopram metabolism [69]. For instance, *CYP1A2* polymorphisms contribute to a faster rate of escitalopram metabolism and are linked to higher rates of fatigue, nausea, and vomiting [33], though no escitalopram dosing recommendations are available based on *CYP1A2* alleles. Additionally, smoking induces greater expression of *CYP1A2*, and smoking increases the rate of escitalopram metabolism, a change which correlates with lower serum concentrations of escitalopram [70]. Patient age and weight may also contribute to differences in the rate of escitalopram metabolism, though the clinical significance of these weight- and age-related metabolic differences remains uncertain [71]. Together, these studies suggest that there may be value in examining the combined effects of multiple P450 genes which may contribute to treatment failure or the development of antidepressant-related hyperarousal.

Genetic polymorphisms that influence SSRI pharmacodynamics may also affect treatment outcomes and rates of adverse events. Alleles of interest include polymorphisms in the gene *HTR2A*, which encodes the serotonin receptor 2A subtype (5-HT_2A_), and *SLC6A4*, which encodes the serotonin transporter protein (5-HTT), the primary pharmacologic target of escitalopram. Studies of the influence of *HTR2A* and other serotonin receptor subtypes on adverse reactions in youth have produced mixed results [69,72,73,74,75], and findings related to *SLC6A4* are similarly equivocal [39,63,64,69]. In light of these ambiguities, some researchers have suggested utilizing a combination of risk alleles to produce more consistent pharmacodynamic results [75]. However, a recent study utilizing combinatorial pharmacogenetics in the treatment of depression in adolescents found no advantage in treatment outcomes or rates of adverse events compared to a control group which did not have access to pharmacogenetic testing [76]. These differences in findings may be due to the mix of antidepressants and doses included in the studies, the lack of accounting for specific antidepressant exposure, differences in alleles tested across studies, and other study design considerations including populations studied and the clinical characteristics of participants.

To date, a few pharmacogenetic studies of *HTR2A* or *SLC6A4* have specifically examined the risk of hyperarousal in youth with a familial risk for BD, though their results are inconclusive. An open trial of citalopram in children and adolescents with depressive or anxiety symptoms found that youth who were homozygous for the “short” allele (S/S) of the *SLC6A4* gene exhibited poor antidepressant treatment response for depressive symptoms (but not for anxiety symptoms) compared to youth who were homozygous for the “long” allele (L/L) of *SLC6A4* [77]. A cross-sectional study of youth with at least one parent with BD found antianxiety medication-naïve S/S youth exhibited greater anxiety than L/L youth [78]. Of particular relevance to our study, the S allele of *SLC6A4* increases the risk that high-risk youth will develop arousal symptoms, an effect which was reportedly mediated by greater activity in, and functional connectivity between, the ventrolateral prefrontal cortex (VLPFC) and the right amygdala [79], elegantly intertwining neurogenetic and neurophysiologic systems (see Figure 1). Although more data are needed to support firm conclusions, we hope that our study will advance our understanding of these and other pharmacogenomic interactions and will do so with a larger number of participants in the context of a randomized placebo-controlled trial. Thus, this study will address broader questions about these genes and the underlying mechanisms of antidepressant-related adverse events.

This study will also serve as an initial step to identifying potential biomarkers which might affect antidepressant treatment response and ultimately, might lead to addressing whether very serious antidepressant-related adverse events that result in antidepressant discontinuation or accelerate the development of BD (i.e., via hyperarousal) are preventable in high-risk youth. Our findings will have basic science, translational, and clinical implications. In addition to advancing the neurobiological understanding of arousal and BD within an RDoC framework, focused genetic screening of high-risk youth may lead to scalable and cost-effective innovations in precision medicine.

## 2. Study Protocol

### 2.1. Setting and Study Population

We will recruit 150, 12- to 17-year-old youth with significant depressive or anxiety symptoms, based on responses to Children’s Depression Rating Scale-Revised (CDRS-R) [81] and the Pediatric Anxiety Rating Scale (PARS) [82] clinical interviews and 60, 12- to 17-year-old healthy control youth (ClinicalTrials.gov Identifier: NCT02553161, first posted 17 September 2015). Youth with significant depressive or anxiety symptoms will be included in our study, and psychotherapy and the study medication (escitalopram) will be provided to study participants to treat their depressive and/or anxiety disorders. Although participants’ DSM-5 diagnoses will be assessed using KSADS, we will not require a specific diagnosis for inclusion and will only exclude participants with the following diagnoses: bipolar I or II disorder, autism spectrum disorders, obsessive compulsive disorder, post-traumatic stress disorder, Tourette’s disorder, or any psychotic disorder including schizophrenia. Our inclusion and exclusion criteria are summarized in Table 1. Healthy controls will receive behavioral, neural, and physiological assessments at baseline only. First-degree relatives will be assessed using the Structured Clinical Interview for Diagnostic and Statistical Manual (SCID) [83] and the Family History-Research Diagnostic Criteria (FH-RDC). We will also compare our findings to those of a recently published double-blind, placebo-controlled trial using the same neuroimaging task and the same medication, but in youth *without* a family history of BD [84].

### 2.2. Randomization

High-risk youth will be randomized to receive double-blinded treatment with psychotherapy plus escitalopram (MED) vs. psychotherapy plus placebo (No MED) in a 2:1 ratio using block randomization with a block size of six. Randomization will be stratified within sites with respect to diagnoses (anxiety only, depression only, or anxiety and depressive symptoms), family history load (i.e., ≥3 first- or second- degree relatives with bipolar disorder vs. 1–2 first- or second-degree relatives with bipolar disorder), and the presence (vs. absence) of concomitant stimulant or alpha-2 agonist treatment. 

We selected psychotherapy (No MED) as the most ethically reasonable comparator for youth presenting with clinically significant symptoms of depression or anxiety. All participants (No MED and MED) will be assigned a study-trained therapist who will provide hour-long, up to weekly, individual cognitive-behavioral therapy or family-focused therapy (FFT) for high-risk youth [87,88]. FFT is a semistructured treatment that is protocol-driven and incorporates psychoeducation about mood and stress vulnerability models for depression/anxiety, structured communication training among family members, and problem-solving skills. Sessions will be weekly for the first 4 weeks, then participants will be given the option to continue meeting weekly or once every two weeks for an additional 12 weeks.

### 2.3. Medication Dosing and Accountability

High-risk youth in the MED condition will be treated with escitalopram and monitored by a child and adolescent psychiatrist who is blinded to treatment assignment. Each high-risk participant will be assessed weekly for the first 4 weeks, then once every two weeks until 16 weeks. Escitalopram will be initiated at 5 mg daily for 1 week, then titrated to 10 mg daily for 1 week, then titrated to a target dose of 20 mg daily (maximum dose 30 mg/day). Titration will proceed no faster than 5 mg/week. Clinicians will carefully monitor participants for treatment response based on symptom severity rating scales of anxiety (PARS), depression (CDRS-R), (hypo)mania (Young Mania Rating Scale) [89], and the emergence of dysfunctional emotional arousal using the clinician-version of the Pediatric Adverse Events Rating Scale (PAERS) [90] and the parent-rated Treatment-Emergent Activation and Suicidality Assessment Profile (TEASAP) [91]. Escitalopram (or placebo) will be discontinued if there is a 2-step worsening on the Clinical Global Impression-Severity of Activation (CGI-SA) scale [91] compared with baseline and a Children’s Global Assessment Scale (CGAS) [92] score of <55.

Adherence, based on pill count, will be obtained at each visit. First, participants will receive weekly clinical follow-ups during dose titration, then clinical follow-ups every two weeks until week 16 to closely monitor for treatment adherence. Blood samples for analysis of serum escitalopram and desmethylescitalopram concentrations will be drawn at 8 weeks or at early termination if sooner than week 8. We aim to recruit medication-naïve youth but recognize that some high-risk youth who are seeking treatment for significant symptoms may be exposed to prior psychotropic medications. We will consider the role of past medications in our analysis of primary outcomes, and participants will be allowed to continue stable doses of concomitant stimulants and alpha-2 agonists. 

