#### 2.4.2. Pharmacogenetic Mediators

Our main pharmacogenetic-related mediators are *CYP2C19* metabolizer phenotype and serum escitalopram level. At 8 weeks or discontinuation of study participation (if earlier), we will obtain a sample for pharmacogenetic testing with the GeneSight Psychotropic assay. *CYP2C19* metabolizer phenotypes will be determined using Clinical Pharmacogenetics Implementation Consortium (CPIC) guidelines [99] and classified as normal (NM), rapid (RM), ultrarapid (UM), intermediate (IM), or poor (PM) metabolizer phenotypes. We will also perform a blood draw at 8 weeks or at early termination to determine serum escitalopram levels via mass spectrometry. Serum escitalopram concentration, *CYP2C19* metabolizer phenotypes, and medication adherence data will be integrated and modelled using MWPharm++ to determine pharmacokinetic parameters such as the maximum serum concentration (C_max_), the 24 h area under the curve (AUC_24_), the elimination half-life (t_1/2_), and clearance (CL) of escitalopram. Genetic testing reports will identify alleles in other genes as well (e.g., *CYP2D6*, *CYP2C9*, *CYP1A2*, *SLC6A4*, and *HTR2A*) and we will explore associations between these alleles and outcomes such as treatment efficacy and rates of adverse events. Based on similar studies of escitalopram in youth [64,65], we predict that high-risk youth with reduced *CYP2C19* metabolizer phenotypes will have higher C_max_ and/or AUC_24_ and higher rates of arousal symptoms than high-risk youth with normal or elevated *CYP2C19* metabolizer phenotypes.

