### 2.6. Limitations

The proposed study will gather data on high-risk youth only during a 16-week period, so this study cannot determine whether there are long-term risks or delayed effects of antidepressant exposure in high-risk youth far beyond the duration of the study. We expect that most children who enroll in our study may still live with their first-degree relatives with BD, so our study cannot easily differentiate between the mental health risks posed by heritable genetic factors as opposed to the stress of living with a family member (especially a parent) with a serious psychiatric disorder. Treatment adherence will be well-tracked, but achieving reliable medication adherence in adolescents remains challenging. Even though minor lapses in medication adherence may have relatively little effect on clinical or neuroimaging outcomes, missed or extra doses may introduce significant noise into pharmacokinetic data. For example, serum escitalopram levels can vary greatly when doses are missed in the week before blood samples are drawn. Furthermore, youth who experience hyperarousal symptoms may be more distressed and consequently less likely to participate in some inherently stressful aspects of the study, such as entering the MR scanner or providing a cheek swab or blood sample for pharmacogenetic analysis. Finally, we expect that most youth enrolled in this study will be medication-naïve, but some study participants may be allowed to take concomitant psychostimulants or alpha-2 agonists before and during the study, and this may also confound results.

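### A pill count at each visit cannot date missed doses, so doses missed just before the single blood draw can be read as faster clearance; a short dose-time record at the draw would help

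*Protocol article*

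**What the plan says.** Section 2.3 names one adherence measure: "Adherence, based on pill count, will be obtained at each visit". It sets the visit schedule as "Each high-risk participant will be assessed weekly for the first 4 weeks, then once every two weeks until 16 weeks", and gives monitoring of adherence as a purpose of the later visits: "then clinical follow-ups every two weeks until week 16 to closely monitor for treatment adherence". The same section provides for "Blood samples for analysis of serum escitalopram and desmethylescitalopram concentrations", which "will be drawn at 8 weeks or at early termination if sooner than week 8".

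Section 2.4.2 says that serum concentration, CYP2C19 phenotype and "medication adherence data will be integrated and modelled using MWPharm++ to determine pharmacokinetic parameters". The listed outputs are C_max, AUC24, "the elimination half-life (t_1/2_), and clearance (CL) of escitalopram". It predicts higher C_max and/or AUC24, and more arousal symptoms, in youth with reduced CYP2C19 metabolism. Section 2.5 makes the escitalopram level a primary mediator, alongside neural change.

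Section 2.6 says adherence will be tracked well. It also says that missed or extra doses may add considerable noise to the pharmacokinetic data, for example because "serum escitalopram levels can vary greatly when doses are missed in the week before blood samples are drawn". It states no measure to reduce this.

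**The concern.** A serum level depends mostly on the last few doses. A pill count returns a total for the interval since the last visit: about 14 days at week 8, and about 7 days for an early-termination draw in the first 4 weeks. Two youths with the same count can have very different levels, depending only on which day was missed. With a single sample and no dose dates, the model has little to separate a recently missed dose from fast elimination.

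At stake are the four derived parameters and the comparison of C_max and AUC24 between CYP2C19 phenotypes. The window that Section 2.6 identifies as critical, the week before the draw, is one the named adherence measure cannot resolve.

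**Working it through.** **The plan's own figures.** The article gives no figure for the pharmacokinetic analysis. Its only power figure (0.82 for d = 0.5, 100 vs 50) reproduces: 0.5/√(1/100 + 1/50) = 2.887; 2.887 − 1.960 = 0.927; Φ(0.927) = 0.823. It concerns amygdala activation and does not bear on this point.

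**Inputs from the article.** Pill count at each visit; two-weekly visits after week 4; one draw at week 8 or at early termination; daily dosing (Sections 2.3 and 2.4.2).

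**Assumptions not in the article.** Half-life h of 20-40 h in step 1 and 15-35 h in step 2; steady state; the draw time stated in each step.

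**Step 1: effect of one missed dose on a trough level.** Let r = 2^(−24/h). The steady-state trough is proportional to r + r² + r³ + …. Omitting the j-th most recent dose leaves the fraction 1 − r^(j−1)·(1 − r). For the last dose (j = 1) this is r. If the last two doses are missed, r² is left.

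| Missed dose | h = 20 h | h = 30 h | h = 40 h |
|---|---|---|---|
| Last dose | 0.435 | 0.574 | 0.660 |
| Last two doses | 0.189 | 0.330 | 0.435 |
| Fourth most recent (j = 4) | 0.953 | 0.919 | 0.902 |
| Eighth most recent (j = 8) | 0.998 | 0.991 | 0.981 |
| 13 days before the last dose (j = 14) | 1.000 | 0.999 | 0.998 |

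The first and last rows have the same pill count, 13/14 = 93%.

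**Step 2: effect on estimated clearance.** One-compartment oral model, absorption rate 0.8/h, known volume V, sample 12 h after the last scheduled dose, k = CL/V. Each dose D given a time t before the draw contributes D·ka/[V(ka − k)]·(e^(−kt) − e^(−ka·t)). The concentration is generated under the true dosing history. CL is then solved so that the model matches it under an assumed history: either full adherence, or the correct two-week pill-count total spread evenly over the 14 days. Ranges are over half-lives of 15-35 h.

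| Doses missed (adherence) | Apparent/true CL with the pill count: the last doses missed | Apparent/true CL with the pill count: the first doses of the 14 missed |
|---|---|---|
| 1 (93%) | 1.50-2.44 | 0.93 |
| 2 (86%) | 2.21-4.44 | 0.86 |
| 3 (79%) | 3.18-6.60 | 0.79 |

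If full adherence is assumed, one missed last dose gives 1.61-2.57. Knowing the correct total therefore changes little (1.50-2.44).

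*Plausibility check at h = 25 h, last dose missed:* the level falls to 2^(−24/25) = 0.51 of its full-adherence value. A roughly inverse relation gives 1/0.51 = 1.96, and scaling by 13/14 gives 1.82. The model gives 1.92 and 1.79.

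**The case against.** **The article is condensed, and the problem is disclosed.** Dose times and the clock time of the draw are details that a full protocol or laboratory manual may hold. A reader might infer that the trial does not record them; the article does not establish that. What stands is narrower. The article names its adherence method, feeds adherence data into the model, concedes the weakness and offers no remedy. If a dose-time form already exists, the sponsor need only say so.

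**Non-adherence is not always read as fast clearance.** A reader might infer a one-way bias. The working shows otherwise: with an evenly spread pill count, misses early in the interval bias clearance downward (0.93, 0.86 and 0.79 times true), and extra doses also act in that direction. The sign depends on timing that the count does not record.

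**The model need not attribute a low level to clearance.** Phenotype enters the model and the metabolite is assayed, so either could limit the error. The article does not say how. The ranges above assume that neither does. If the fit leaned heavily on phenotype, the later comparison of phenotype with model-derived exposure would be partly circular.

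**A dose record does not repair the measured level.** Section 2.5's mediator is the escitalopram level. A better dosing history improves the derived parameters but leaves a level lowered by a missed dose unchanged. The CYP2C19 phenotype comes from a genetic assay and does not depend on adherence, so the phenotype-arousal comparison is not exposed to this error.

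**No bias linked to arousal is shown.** A reader might suppose that aroused youth skip more doses, which would work against the hypothesis. Section 2.6 says only that distressed youth may be less willing to be scanned or to give samples; it does not say that they miss doses.

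**The size is a single-patient contrast.** The article gives no frequency of recent misses, so the loss of power or precision in any planned analysis cannot be calculated.

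**Conclusion.** The point holds as an inexpensive improvement, not as an error that invalidates an analysis. The only adherence measure named gives totals over about two weeks at week 8, or one week for early-termination draws in the first 4 weeks, and cannot date a miss. Under the stated assumptions (half-life 15-35 h, one compartment, known volume, no constraint from phenotype or metabolite), one missed last dose is read as clearance about 1.5-2.4 times true. One miss at the start of a two-week interval is read as about 0.93 times true. The direction for recent misses does not depend on the assumed half-life; the size does. The consequence is added error in C_max, AUC24, half-life and clearance, and so in the CYP2C19-exposure analysis. The documents do not support a claim of general upward bias in clearance, or a claim that a better dosing history would correct the serum-level mediator.

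**What to change.** 1. At the week-8 or early-termination draw, record the date and time of each dose over the preceding 7 days, the current prescribed dose and the clock time of the draw. Seven days is enough under the step 1 assumptions: a single older miss changes the trough by at most about 2%.
2. Use this record together with the pill count, not in place of it, as the dosing history in MWPharm++. The count provides a check on the recalled total.
3. Because the measured level cannot be corrected this way, add a sensitivity analysis of the serum-level mediator that excludes youth who missed a dose in the last 3 days. In step 1, a single miss just outside that window still leaves 0.90-0.95 of the trough. The excluded group is defined by behaviour after randomization, so the result should be read only as a sensitivity check.
4. State briefly how phenotype and metabolite enter the fit.

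Cost: one short form at an existing visit and one additional analysis, with no added visit or assay. Downside: recall over 7 days is imperfect, so the record reduces the timing error but does not remove it.
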